### Sample size

Previous studies using pre/post EA total sum scores to compare the effectiveness of parent-child interventions [47,48] have reported medium to very large (0.5–1.17) effect size according to Cohen’s [49] criteria. The study is powered to detect a large between-group effect size of Cohen’s d = 0.8 in the primary outcome of change in EA total sum scores between baseline and post-intervention. With a significance criterion of α = 0.05 and power = 80%, the minimum sample size is n = 52 with n = 26 in each sample. Assuming drop-out does not exceed 10%, the aim is to recruit 60 families in total. Furthermore, given the nature of the study involving a short-term home-delivered intervention, n = 30 families in the JP intervention group seems to be a feasible yet significant number.

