## Data analyses

### Quantitative data

Univariate statistical analysis will be used to compare demographic and baseline variables between condition groups. To assess the effects of the interventions, a Linear Mixed-Effects Model (LMM) using a Restricted Maximum Likelihood (REML) approach, including time (pre vs. post), group (JP intervention vs. control), and their interaction, will be used. The covariates of the child’s gender and the VABS-3 score will be adjusted based on both clinical and statistical relevance. To assess associations between EA and IPS to parent and child playfulness scores, Spearman’s correlation coefficients will be calculated. To examine whether the playfulness scores of parents and children (each score entered separately) mediate the relationship between the intervention and the change scores of the primary outcome of EA total sum scores and IPS, Hayes’s [66] PROCESS macro will be used, selecting model 4, 5, 7, or 14 based on the relationship between the covariates involved and the study variables. We acknowledge that, using multiple regression with three to four predictors (the treatment group, parents’/child’s playfulness score, children’s VABS-3 score, and gender), and considering an alpha level of .05, a power of .80, and an effect size of f² = .02, a sample size of 59–65 participants is required (see Daniel Soper’s calculator for a priori sample size [67]). Consequently, given our modest sample size of n = 60, the proposed mediation analyses should be regarded as exploratory and interpreted with caution. Moreover, to minimize the risk of overfitting, only covariates with both theoretical and statistical justification (e.g., child’s VABS-3 score, gender) will be incorporated into the model, and indirect effects will be estimated via bootstrap confidence intervals.

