## Discussion

The study will discuss the results and clinical applicability of the findings regarding the importance of play and playfulness for the population of children with ID and their mothers. The extensive literature on the importance of play for children’s development and the value of playfulness for the parent-child relationship, supports the hypothesis that enhancing play and playfulness of children with ID and their mothers will contribute positively to the quality of their interactions. Therefore, the JP intervention will focus on enhancing parent-child playfulness, while examining its role as a mechanism of change in parent-child interactions. In order to promote playfulness, the JP intervention will utilize CAT and their unique characteristics to facilitate non-verbal, creative, and reciprocal dyadic play. By shifting the focus from behavior management to fostering playfulness and mutual engagement, JP aims to fill an existing gap in early intervention programs for children with ID and their parents.

The study has several limitations: First, although the sample size is powered to detect the expected effects, a larger sample would be recommended in future research. Second, the relatively short duration of the interventions may limit their impact on the outcome measures. Third, participants are not blinded to their assigned condition. Fourth, the inability to fully control for the influence of external factors, such as additional treatments, may confound the results.

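### The mediation power statement pairs f² = .02 with 59–65 participants, but 59–65 is the requirement at f² = .20; the two figures must be reconciled

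*Protocol article*

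**What the plan says.** The Quantitative data section plans mediation analyses with the PROCESS macro on change in EA and IPS, and then gives a sample-size statement for the regressions behind them.

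- Model: "using multiple regression with three to four predictors", listed as "the treatment group, parents’/child’s playfulness score, children’s VABS-3 score, and gender".
- Error rates: "considering an alpha level of .05, a power of .80".
- Result: "an effect size of f² = .02, a sample size of 59–65 participants is required", credited to an online "calculator for a priori sample size".
- Conclusion drawn: "given our modest sample size of n = 60, the proposed mediation analyses should be regarded as exploratory and interpreted with caution".

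Two other places bear on how the figure is read. The Sample size section, which powers the primary outcome for d = 0.8 on EA change, says: "Assuming drop-out does not exceed 10%, the aim is to recruit 60 families in total". The limitations paragraph of the Discussion says, "although the sample size is powered to detect the expected effects", a larger sample would be advisable in future work.

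**The concern.** An f² of .02 is a very small effect for a multiple regression: the predictors together explain about 2% of the variance (R² = .02/1.02 = .0196). A requirement of about 60 participants for 80% power at that size is implausible on its face.

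The figure also carries weight in the text. The caution about the mediation analyses follows directly from comparing n = 60 with 59–65. Because 60 lies inside that range, a reader learns that the trial is borderline for a small effect, when it is borderline only for an effect about ten times larger on the f² scale. Mediation by playfulness is the third study hypothesis, so a null result there will be interpreted, and this sentence tells the reader how much such a result means.

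**Working it through.** **Inputs.** From the Quantitative data section: alpha = .05, power = .80, p = 3 or 4 predictors, f² = .02, planned N = 60. From the Sample size section: drop-out of at most 10%. The mediation outcomes are change scores and so need post-intervention data; analysable N therefore runs from 60 × 0.9 = 54 up to 60.

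**Formula.** For the overall F test of a multiple regression, the numerator df is u = p, the denominator df is v = N − p − 1, and the noncentrality is λ = f² × N. Power = P[F′(u, v, λ) > F(.95; u, v)], where F′ is noncentral F. The required N is the smallest with power ≥ .80.

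**Step 1: try to reproduce 59–65 at f² = .02.**

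| Reading of the stated inputs | p = 3 | p = 4 |
|---|---|---|
| Overall test, f² = .02, λ = f²·N | 550 | 602 |
| Overall test, f² = .02, λ = f²·v | 554 | 607 |
| One coefficient, f² = .02, two-sided | 395 | 395 |
| One coefficient, f² = .02, one-sided | 311 | 311 |
| .02 read as R² (f² = .02/.98 = .0204) | 539 | 590 |
| f = .2 (f² = .04) | 277 | 304 |

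None is close to 59–65.

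**Step 2: find the f² that gives 59–65.**

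| f² | p = 3 | p = 4 |
|---|---|---|
| .15 | 77 | 85 |
| **.20** | **59** | **65** |
| .25 | 48 | 53 |

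At f² = .20 both ends of the printed range are matched exactly: N = 59 with p = 3 has λ = .20 × 59 = 11.8 and power .803; N = 65 with p = 4 has λ = .20 × 65 = 13.0 and power .803. One participant fewer gives .795 in each case.

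**Step 3: power the trial has.**

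| | N = 54, p = 3 | N = 54, p = 4 | N = 60, p = 3 | N = 60, p = 4 |
|---|---|---|---|---|
| λ at f² = .02 | 1.08 | 1.08 | 1.20 | 1.20 |
| Power at f² = .02 | .116 | .104 | .124 | .112 |
| Power at f² = .20 | .76 | .71 | .81 | .76 |
| f² detectable at 80% power | .218 | .243 | .195 | .217 |

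**Size of the discrepancy.** It is a factor of .20/.02 = 10 in effect size. In N it is 550/59 = 9.3 with three predictors and 602/65 = 9.3 with four.

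**Scope of the calculation.** All of this concerns the overall R² of the regression. The mediation analysis tests an indirect effect (the product of the treatment-to-playfulness and playfulness-to-outcome paths) by bootstrap. Its power depends on those two paths, for which the document gives no values.

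**The case against.** The strongest reply is that nothing depends on this number. The same sentence presents it as an acknowledged limitation and goes on to call the mediation analyses exploratory. N = 60 comes from the d = 0.8 calculation for EA change, which does not use f². The exact match at .20 suggests that the participant numbers were computed correctly and only the printed effect size is wrong. All of this stands. It settles how serious the point is, but the published sentence is still wrong: the exploratory label remains, while the reason given for it misstates how far short the sample would be for a small effect.

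A reader might infer four stronger points that the document does not support.

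- **That the sample size itself is wrong.** The match at f² = .20 points to the effect size instead. The document does not show which value was intended.
- **That 54 completers are expected.** The plan assumes drop-out of no more than 10%, so 54 is the floor of that assumption. Results belong on the range 54–60.
- **That the Discussion claims adequate power for mediation.** The words "although the sample size is powered to detect the expected effects" can be read as referring only to the d = 0.8 calculation, and the Quantitative data section already withholds such assurance from the mediation analyses.
- **That power for the indirect effect must be lower than for overall R².** The ordering depends on the unstated paths. An illustrative simulation at n = 54, with an assumed treatment effect on playfulness of 0.8 SD and an assumed playfulness-to-outcome path of 0.14 (f² about .02), gave about 13–14% for the indirect effect against 10–12% for overall R², which is the reverse.

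**Conclusion.** The concern holds as an internal inconsistency. With three to four predictors, alpha .05 and power .80, f² = .02 requires 550–602 participants; 59–65 is the requirement at f² = .20. A decimal slip in the printed effect size is the likelier explanation, but only the sponsor can confirm it. If f² = .02 was meant, power with 54–60 analysable dyads is about 10–12%. If .20 was meant, it is 71–81%, depending on drop-out and the number of predictors.

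These results assume the overall regression F test, which is what a standard a priori calculator for multiple regression addresses. The single-coefficient and R² readings that were tried do not rescue the printed pair. The primary analysis, its sample size and the conduct of the trial are untouched, and the mediation is already declared exploratory. It is a minor but real correction, not a must-fix.

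**What to change.** In Data analyses, Quantitative data:

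1. Confirm the intended effect size and print a consistent pair: f² = .20 with 59 (three predictors) to 65 (four), or f² = .02 with 550 to 602.
2. Add that with 54–60 analysable dyads (0–10% drop-out) the f² detectable at 80% power is about .19–.22 with three predictors and .22–.24 with four.
3. Note that these figures concern overall R² and not the bootstrapped indirect effect, without saying which has the lower power.
4. Keep the exploratory label.

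Optionally, make clear in the Discussion's limitations that the power claim refers to d = 0.8 on EA change.

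The cost is wording only: no change to sample size, data collection or analysis method. The stated figure becomes less favourable. Recruitment is still open and results are due in September 2026, so the correction can be made before any mediation result is interpreted.

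### Mediation covariates must pass an undefined statistical condition as well as a theoretical one, so a real confounder of the playfulness-to-outcome path can be left out

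*Protocol article*

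**What the plan says.** The Protocol article, Data analyses, Quantitative data, gives a covariate rule twice.

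- Mixed model: "The covariates of the child’s gender and the VABS-3 score will be adjusted based on both clinical and statistical relevance".
- Mediation models: "only covariates with both theoretical and statistical justification" are to enter, with VABS-3 and gender given as examples. The reason given is to limit overfitting.

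Neither sentence names a test or a threshold. The mediation models are described as "using multiple regression with three to four predictors", with four candidates listed: treatment group, one playfulness score, VABS-3 and gender. For the test itself, "indirect effects will be estimated via bootstrap confidence intervals". The same paragraph calls the mediation analyses exploratory because of the modest sample. The third item under Study hypotheses nevertheless states mediation as a hypothesis, and the Discussion expects findings on playfulness as a mechanism of change.

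**The concern.** The mediation rule asks for theory and statistics together, so a covariate that is justified on theory alone can be excluded. That is the wrong way round for the second half of a mediation model. Group is randomised, but playfulness is not. Its association with EA or IPS can be read as an effect only if common causes of both are adjusted for, and this need does not depend on whether a covariate reaches significance in a small sample.

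VABS-3 is a plausible common cause. The Background describes play as limited by developmental level, and adaptive level could also bear on change in interaction quality. If VABS-3 is screened out, its contribution is attributed to playfulness, and the bootstrap interval is computed as though no selection had taken place. What is at stake is the mechanism claim, not the primary comparison.

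**Working it through.** **Inputs from the document.** 60 dyads, 1:1 allocation, drop-out up to 10%, d = 0.8, α = .05 (Sample size; Study procedures). The plan states no figure for covariate selection. Its sample size, the source of n here, does reproduce: a two-sided t-test needs 25.5, so 26 per arm and 52 in total; 52/0.9 = 57.8, so 58, rounded up to 60. With 10% loss, 60 × 0.9 = 54 dyads.

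**Assumptions, since the document gives none.** One baseline confounder C, standing for VABS-3. Within-arm correlation of C with playfulness r_CM = .3 to .5, and with EA change r_CY = .2 to .4. An intervention effect of 0.8 SD on playfulness and on EA change. True playfulness-to-EA effect of zero. Any screen uses p < .05.

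**Step 1: bias when C is left out.** With unit within-arm variances, the playfulness coefficient has expectation r_CM × r_CY instead of 0.

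- Low end: .3 × .2 = .06. Spurious indirect effect 0.8 × .06 = 0.048 SD.
- High end: .5 × .4 = .20. Spurious indirect effect 0.8 × .20 = 0.16 SD.

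If one correlation is negative, the product and the bias are negative.

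**Step 2: false positives when C is left out.** For the test of the playfulness coefficient, z shifts by about ρ√(n − 3)/√(1 − ρ²), where ρ is that product.

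- n = 60, ρ = .06: .06 × 7.55/.998 = 0.45, giving about 7%.
- n = 60, ρ = .20: .20 × 7.55/.980 = 1.54, giving about 34%.

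Under randomisation an imbalance test keeps C only about 5% of the time, so that screen is close to never adjusting: .95 × 34% + .05 × 5% ≈ 32.5% at the high end.

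**Step 3: simulation over the assumed range, n = 54 and 60.**

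| Rule for entering C | False positives |
|---|---|
| Always | 4–5% |
| Kept if associated with the outcome | about 4–6% |
| Kept if significant in the outcome model containing playfulness | 7–11% |
| Kept if arms differ at baseline | 7–31% |

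**Step 4: independent simulation with the percentile bootstrap interval for the indirect effect** (n = 60, effect on playfulness 0.8 SD, same correlation r with both variables).

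| r | Always | Outcome screen | Outcome-model screen | Imbalance screen |
|---|---|---|---|---|
| .2 | 4.1% | 4.9% | 5.9% | 6.1% |
| .3 | 5.0% | 5.2% | 7.1% | 9.9% |
| .4 | 4.7% | 5.3% | 7.5% | 20.4% |

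At r = .3, C was dropped about 41% of the time by the outcome screen, 40% by the outcome-model screen and 94% by the imbalance screen. Requiring significance with both playfulness and outcome dropped it 63% of the time and gave 5.7%. With 1,500 to 2,000 runs per cell, the simulation error is about one percentage point (at 2,000 runs, 2 × √(.05 × .95/2000) ≈ .01).

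**Step 5: conditions.** If the intervention does not move playfulness, the rate stays below 2% under every screen. With correlations of .5 and −.4, false rejections fell mainly on the negative side (7.5–9.2% against 2.1–2.7%).

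**Step 6: the overfitting reason.** Four predictors in 54 to 60 dyads give 54/4 = 13.5 to 60/4 = 15 dyads per predictor. Two named covariates are affordable without a screen.

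**Step 7: the mixed model.** In a simulated complete data set, the time-by-group estimate was 0.5637 with and without a time-invariant covariate. A child-level main effect cancels from the comparison of changes.

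**The case against.** The strongest reply is that the document contains no step that drops covariates. VABS-3 and gender can be read as the two already chosen because they meet both standards, and a working definition of the statistical part could sit in an analysis plan that is not shown. The first part of this stands: no p-value rule is written, and nothing selects one reading over another. But the article does state a rule, and that rule makes a statistical condition necessary. The examples are open-ended, and a count of three to four predictors fits conditional entry.

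A reader might infer more than the text supports:

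- **That covariates are removed when non-significant.** This is one natural reading, not the text. Under a screen on association with the outcome, the inflation is negligible.
- **That the analyst may pick whichever covariate set gives the best result.** The plan does not permit selection by result, so error rates for such picking do not describe it.
- **That the bias favours the playfulness hypothesis.** The direction depends on correlations that the document does not give. The outcome is a change score, and less able children could gain more.
- **That the primary result is at risk.** With complete data the time-by-group estimate does not move.
- **That the univariate baseline comparison chooses the covariates.** It is planned, but nothing links it to covariate entry.

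The exploratory label also stands, so no confirmatory error rate is affected. It is a warning about a modest sample, however, and does not remove bias from an omitted confounder.

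**Conclusion.** The point holds for the mediation models only. An undefined statistical condition on covariate entry can exclude a confounder that theory says belongs in the unrandomised playfulness-to-outcome path. The consequence ranges from negligible to serious with the meaning given to *statistical*: against about 5% under fixed adjustment, about 5% (outcome screen), 7–11% (outcome-model screen) or 7–31% (imbalance screen).

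These figures rest on the assumed correlations, a p < .05 screen, an intervention that does move playfulness (as the study hypothesises) and a true mediator effect of zero. They show what the wording allows, not what will happen. Because the primary estimate is unaffected and the analysis is exploratory, this is a cheap improvement and not a threat to the trial's main conclusion.

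**What to change.** Delete the statistical condition from the mediation rule. State that VABS-3 and gender enter every mediation regression, for the mediator and for the outcome, whatever their p-values. Use the same fixed pair in the mixed model in place of the clause that they "will be adjusted based on both clinical and statistical relevance". The reason there is consistency, since the estimate does not change with complete data.

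The cost is a wording change and one or two degrees of freedom per model. Under Status and timeline, recruitment is expected to run to June 2026, so the set can be fixed before the analysis. Fixing it removes a data-driven choice. It does not guarantee that VABS-3 and gender are the only confounders, so the cautious interpretation should stay.

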### Qualitative data

To explore mothers’ subjective lived experiences of the JP intervention, an Interpretative Phenomenological Analysis (IPA) methodology will be employed to analyze the data collected from the semi-structured interviews [50]. This approach will facilitate the in-depth exploration of the mothers’ experiences during the participation in the JP dyadic intervention through a double hermeneutic – a dual interpretative process in which the researcher will seek to make sense of the mothers’ own sense-making [50]. IPA’s idiographic orientation will allow detailed examination of each mother’s experience while accommodating heterogeneity in how the dyadic intervention was perceived, rather than assuming uniform effects. Interview analysis will follow IPA procedures, progressing from case-level interpretations to patterns of convergence and divergence across participants, with reflexive consideration of the researcher’s role, thereby complementing the study’s quantitative outcomes.

The two-month follow-up interview will use Interpersonal Process Recall (IPR) procedure, a qualitative, interview-based method designed to access participants’ conscious yet unspoken experiences during the original interaction [52]. In this approach, the interaction of interest – here, a dyadic session – will be video-recorded and subsequently reviewed with the mother and the researcher interviewer. The IPR procedure will explore mothers’ recollections of their thoughts, feelings, and emotions as they occurred during the recorded session, aiming to reveal internal processes that may not have been previously articulated [68].

### Status and timeline

The study is currently ongoing, beginning in February 2024 and 40 participating dyads have been recruited. 30 have completed the study while the rest are ongoing. Participant recruitment is expected to be completed by June 2026 and full results will be available by September 2026.

## Discussion

The study will discuss the results and clinical applicability of the findings regarding the importance of play and playfulness for the population of children with ID and their mothers. The extensive literature on the importance of play for children’s development and the value of playfulness for the parent-child relationship, supports the hypothesis that enhancing play and playfulness of children with ID and their mothers will contribute positively to the quality of their interactions. Therefore, the JP intervention will focus on enhancing parent-child playfulness, while examining its role as a mechanism of change in parent-child interactions. In order to promote playfulness, the JP intervention will utilize CAT and their unique characteristics to facilitate non-verbal, creative, and reciprocal dyadic play. By shifting the focus from behavior management to fostering playfulness and mutual engagement, JP aims to fill an existing gap in early intervention programs for children with ID and their parents.

The study has several limitations: First, although the sample size is powered to detect the expected effects, a larger sample would be recommended in future research. Second, the relatively short duration of the interventions may limit their impact on the outcome measures. Third, participants are not blinded to their assigned condition. Fourth, the inability to fully control for the influence of external factors, such as additional treatments, may confound the results.

Despite these limitations, this study is expected to contribute to the body of research of early interventions for children with ID and their parents, advocating for play-centered approaches and employing CAT. As the application of CAT to support dyadic relationships in early childhood is an emerging area of research, this study is expected to contribute valuable insights to the existing body of knowledge in this field by providing evidence of the effectiveness of dyadic CAT-based interventions in improving mother-child relationships in children with ID. Furthermore, the study findings will shed light on playfulness as a mechanism of change in interactions between children with ID and their mothers, thus informing how CAT can benefit parent-child relationships in this population. The qualitative data will offer a maternal perspective on the intervention’s most valuable components and its long-term impact on daily dyadic interactions and parenting experiences. Eventually, the study findings can contribute to the establishment of an evidence-based manual, as well as guidelines for practitioners working with this population.
